#### Dual-target stimulation

2.3.1

The left M1 and right cerebellar hemisphere will be selected for dual-target stimulation. The resting motor threshold (RMT) and active motor threshold (AMT) will be assessed during the first treatment session. The patient will be positioned supine, with fingers relaxed and palms facing upward. Preliminary stimulation will be administered at 70% of the maximum output intensity of TMS, while observing the contraction of the contralateral thumb (abductor pollicis brevis) to identify the optimal stimulation site capable of eliciting motor-evoked potentials (MEP) in the abductor pollicis brevis muscle. The stimulation intensity will then be gradually decreased to determine the RMT, defined as the minimum stimulation intensity required to produce a slight contraction of the contralateral abductor pollicis brevis in 5 out of 10 attempts (with evoked thumb abductor potentials of 50 microvolts amplitude or more) (33–35). While AMT is defined as the lowest stimulus intensity that elicited a peak MEP amplitude of ≥200 microvolts amplitude during a 10% Maximum Voluntary Contraction (MVC) of the dorsal interosseous muscle of the first interosseous (right-hand side). This criterion must be met in at least 5 consecutive trials out of 10 (36, 37).

A figure-eight coil will be utilized in conjunction with a magnetic-field stimulator (Mag TD 40, Factory No. 44777533). The specific operational procedures will be conducted in accordance with the TMS operation guide (38). The operator will consist of qualified TMS treatment professionals from the First Affiliated Hospital of Xi’an Jiaotong University, who have undergone both theoretical and practical training, enabling them to independently administer TMS treatment to a designated number of patients.

In this study, we will localize the left M1 area according to the international Electroencephalogram (EEG) 10–20 system electrode placement, the specific positioning is shown in Table 2. cTBS uses triplets of stimuli at 40 Hz, repeated every 200 ms for 40 s. The stimulation parameters for the right cerebellar hemisphere are as follows, over a period of 10 days, a total of 90 repetitions of 900 pulses will be administered at a frequency of 1 Hz, with each stimulation period lasting 10 s followed by a 2-s interval. We will apply 1 Hz rTMS to stimulate the right cerebellum, followed by cTBS to stimulate the M1 region in a sequential intervention. To ensure accurate stimulation, the patient will be positioned supine on the treatment bed, maintaining a still head position while the device is securely fixed on the head above the designated stimulation target.

**Table 2 tab2:** Location of the stimulus target.

Stimulus target	Location
Left M1 region	Above the left cerebral hemisphere M1 area (C3, International electroencephalogram 10–20 system), perpendicular to the central sulcus (45° from the midline of the hemisphere)
Right cerebellar hemisphere	1 cm below the occipital eminence, 3 cm to the right parietal

In rTMS studies, stimulation intensity is based on the Motor Threshold (MT), typically ranging from 80 to 120% of RMT to achieve desired neural effects safely (39). For cTBS, the standard intensity is 80% of the AMT, effectively inducing long-term inhibitory effects while ensuring participant safety (40). We select a stimulation intensity of 90% of the RMT for 1 Hz rTMS and 80% of the AMT for cTBS, based on previous research (26, 27, 29, 32, 33).

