**Methods:**

Twenty-four patients with ET will be randomly assigned to three groups: dual-target stimulation, single-target stimulation, or sham stimulation. The single-target stimulation group will receive stimulation of the right cerebellar hemisphere for 10 days, whereas the dual-target stimulation group will be given stimulation of both the left M1 cortex and the right cerebellar hemisphere. The sham stimulation group will be given sham stimulation for 10 days. Tremor will be assessed using both the subjective The Essential Tremor Rating Assessment Scale (TETRAS) and objective accelerometer-based tremor analysis. at baseline (before stimulation), after the first, fifth, tenth days of treatment (D1, 5, 10), 24 h after 10 days of treatment (D10-24 h), and 1, 2, 3, and 4 weeks after stimulation (W1, 2, 3, 4).

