#### Single-target stimulation

2.3.2

Patients assigned to the single-target stimulation group will receive real stimulation to the right cerebellar hemisphere and sham stimulation to the left M1 cortex, utilizing the same methods and stimulation parameters as previously described.

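### The cerebellar rTMS dose cannot be followed as worded, and even its one coherent reading leaves 900 pulses per day and 900 per course both open, a 10-fold difference

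*Protocol article*

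**What the plan says.** The cerebellar dose is set in one sentence of Section 2.3.1 (Dual-target stimulation). It says that "a total of 90 repetitions of 900 pulses will be administered", ties that total to the length of the course ("over a period of 10 days, a total of 90 repetitions of 900 pulses"), sets the rate at 1 Hz, and adds the train pattern, "with each stimulation period lasting 10 s followed by a 2-s interval".

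Section 2.3.2 applies this to the second active arm, which is treated "utilizing the same methods and stimulation parameters as previously described". The Methods part of the abstract confirms the length of the course: "The single-target stimulation group will receive stimulation of the right cerebellar hemisphere for 10 days".

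No other section gives a daily pulse count, a course total or a session length for the cerebellar component. Section 2.10 (Blinding) describes two rounds of stimulation but attaches no pulse count to either. Section 2.3.3 later offers all groups a further 10 days of open-label cerebellar rTMS without separate parameters.

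**The concern.** The sentence joins a repetition count, a pulse count, a frequency, a train length and a number of days, but it does not say what a repetition is or what period the 900 pulses cover. Read word for word, it has 900 pulses in each repetition and 90 repetitions across the whole course. That does not sit with a 10 s train at 1 Hz.

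This is the only pulse count given for the cerebellar treatment, which is the whole of the active treatment in the single-target arm and half of it in the dual-target arm. Safety and feasibility are stated aims, and Section 2.8 says the results will inform a Phase 3 trial. Statements about tolerability, and any attempt to repeat the regimen, need a dose that can be read from the text. The adherence measure in Section 2.7.2 would not resolve the matter, because it counts completion of the 10-day course within 12 days and carries no pulse criterion.

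**Working it through.** **Inputs, all from Section 2.3.1:** frequency 1 Hz; 10 s on and 2 s off, so a 12 s cycle; 90 repetitions; 900 pulses; 10 days.

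**Step 1. Reproduce the stated figure.**
- Pulses per train = frequency × train length = 1 × 10 = 10.
- 90 trains × 10 pulses = 900 pulses, which matches the stated 900.
- Duration = 90 × 12 s = 1,080 s = 18 min.

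So 90, 900, 1 Hz and 10 s agree exactly if a repetition is a 10 s train and 900 is the sum over 90 trains.

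**Step 2. Take the wording literally, with 900 pulses in each repetition.**
- If a repetition is the 10 s period, 900 pulses in 10 s is 900 / 10 = 90 Hz, not 1 Hz. At 1 Hz, 900 pulses need 900 s. This reading is impossible.
- If a repetition is a 900-pulse block made of many trains, the course is 90 × 900 = 81,000 pulses. Per day this is 81,000 / 10 = 8,100 pulses, or 8,100 / 10 = 810 trains. At 12 s each, that is 9,720 s = 162 min = 2.7 h a day. This reading does not contradict itself, but it implies a very long daily session before any M1 stimulation is added.

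**Step 3. Take the coherent reading (repetition = 10 s train) and ask what period 900 covers.**

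| Reading | Pulses per day | Trains per day | Time per day | Course total |
|---|---|---|---|---|
| 900 is the 10-day total | 900 / 10 = 90 | 9 | 9 × 12 s = 1.8 min | 900 |
| 900 is the daily figure | 900 | 90 | 90 × 12 s = 18 min | 900 × 10 = 9,000 |

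Ratio: 9,000 / 900 = 10.

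The grammar favours the first row, since the total is tied to the 10-day period, but nothing elsewhere in the article confirms either row.

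**The case against.** The strongest reply is that the arithmetic is sound: 90 trains of 10 pulses give 900 pulses in 18 minutes, so the fault is one of wording. This stands, and it limits the point. It does not remove it, because that reading changes what the sentence says and still leaves the time basis open.

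Three stronger readings are tempting and are not supported.

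- **A 90-fold ambiguity.** A reader might set 81,000 against 900 and report a factor of 90. The 81,000 figure needs a repetition to be a 900-pulse block, whereas the conflict with the 10 s train needs a repetition to be that train. The two cannot be claimed together. Once a repetition is a train, 81,000 drops out and the span is 10-fold.
- **Operators delivering different doses.** The article describes one hospital, one identified stimulator, a TMS operation guide and trained operators. Nothing shows that anyone sets pulse counts from this sentence, or that the delivered dose is unknown to the trial team.
- **Pulse recording is absent.** Section 2.1 says that daily treatment completion is recorded. Finer data capture is commonly left to the full protocol or case report form, so its absence from an article is no finding.

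It could also be said that an article condenses a fuller protocol. That excuses what is left out. Here the dose is stated, in words that cannot be followed.

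**Conclusion.** The sentence is wrong as written and must be reconciled. Its literal form is either impossible or implies 81,000 pulses at 2.7 h a day. Its one coherent form, 90 trains making 900 pulses, leaves the course total at either 900 or 9,000 pulses, a factor of 10, in both active arms.

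The factor of 10 rests on two assumptions: that a repetition is the 10 s stimulation period, and that treatment is spread evenly over 10 days. The article does not show which figure is right. The finding concerns the stated dose; it is not evidence that treatment has been delivered inconsistently.

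**What to change.** Rewrite the sentence in Section 2.3.1 so that it gives pulses per train, trains per session, sessions per day, pulses per session and course total, and so that these multiply out. Section 2.3.2 then inherits the correction. Say also whether the open-label course in Section 2.3.3 uses the same parameters.

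Check the corrected figures against the programme set on the stimulator. Patients were already being recruited when the article was submitted, so the text should describe what is actually being given. Which reading is correct is for the sponsor and the investigators to establish.

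The cost is one corrected sentence and one check of the device programme. The design, sample size and analysis are unaffected.

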#### Single-target stimulation

2.3.2

Patients assigned to the single-target stimulation group will receive real stimulation to the right cerebellar hemisphere and sham stimulation to the left M1 cortex, utilizing the same methods and stimulation parameters as previously described.

#### Sham stimulation

2.3.3

Patients assigned to the sham-stimulation group will receive sham stimulation targeting the left M1 cortex and the right cerebellar hemisphere. This procedure mimics the characteristics of actual stimulation by reversing the coil by 90 degrees; however, it does not produce an effective stimulus.

To ensure the rights of our participants, we will provide an additional 10 days of open-label right cerebellar hemisphere rTMS to all groups 1 month after the completion of all interventions and the four-week follow-up period, as a form of ethical compensation. Informed consent will be obtained from all participants prior to the initiation of the study.

### Accelerometer-based tremor analysis

2.4

Patients will be positioned in a comfortable chair equipped with armrests, and both upper limb tremor movements will be recorded utilizing a multi-sensor signal accelerometer (chip model: MPU6500). The device will be affixed to the dorsal surface of the metacarpal bones of both hands, enabling the capture of resting tremor (the patient will be instructed to relax and rest their hands on the chair armrests), postural tremor (two specific poses will be required: one with the arms extended forward and parallel to the ground, and the other maintaining a wing-beat posture), and kinetic tremor (assessed through the finger-nose test). Each movement will be recorded for 20 s, with tremor measurements repeated twice at each time point. The average of the two recordings will subsequently be calculated.

### Brain imaging

2.5

Resting-state functional magnetic resonance imaging (Rs-fMRI) images, three-dimensional (3D) T1-weighted images, and conventional T2-weighted images will be acquired using a 3.0 Tesla MRI system (Philips, Netherlands, Model: Ingenia 3.0T CX, Serial Number: 78356). Foam pads provided by the manufacturer will be employed to minimize motion-related interference, and earplugs will be inserted into both external auditory canals to mitigate auditory stimulation. During the scanning procedure, participants will be instructed to keep their eyes closed and remain awake.

Rs-fMRI will be conducted utilizing an echo-planar imaging (EPI) pulse sequence with the following parameters: 48 slices, slice thickness/gap of 3.5/0 mm, repetition time (TR) of 2,000 ms, echo time (TE) of 30 ms, flip angle (FA) of 90°, and a field of view (FOV) of 256 × 256 mm. Additionally, 3D T1-weighted images will be acquired with parameters including the shortest TR and TE, a flip angle of 12°, a FOV of 256 × 256 mm, a matrix of 256 × 256, and a total of 194 slices. Conventional T2-weighted images will also be obtained, characterized by a TR of 3,000 ms, a TE of 80 ms, a slice thickness/gap of 5.0/1 mm, a FOV of 230 × 209 mm, and a total of 27 slices. It is important to note that while the conventional T2-weighted images will not be utilized for data processing, they will be employed for image evaluation purposes.

All functional imaging data preprocessing will be conducted utilizing the Statistical Parametric Mapping (SPM12) and Data Processing & Analysis for Brain Imaging (DPABI) software, both of which operate on the Matrix Laboratory platform (Matlab Release 2023b). The main steps of image preprocessing are as follows: (i) the initial 10 volumes will be removed to mitigate T1 equilibrium effects; (ii) slice-timing correction will be applied; (iii) subsequent functional images will be realigned to the first volume to correct for within-run head motion; (iv) T1-weighted images will be co-registered to the mean Rs-fMRI data for each subject. Specifically, SPM Diffeomorphic Anatomical Registration Through Exponentiated Lie Algebra (DARTEL) segmentation will be employed to partition the 3D T1-weighted images into probability maps for gray matter (GM), white matter (WM), and cerebrospinal fluid (CSF). All GM, WM, and CSF images will be resampled and normalized to the Montreal Neurological Institute (MNI) space. (v) Nuisance covariates, including WM signal, CFS, and the mean time series of the entire brain, will be regressed out; (vi) first-order polynomial functions will be utilized to eliminate linear trends; (vii) a filter will be applied to reduce low-frequency drift and high-frequency noise; and (viii) smoothing will be performed (41, 42). Functional connectivity (FC) analysis will be based on the pre-processed images.

This study will employ Independent Component Analysis (ICA) to assess the FC of CTC circuits, the Default Mode Network (DMN), and additional networks, including executive, frontoparietal, auditory/language, and visual networks. FC can be evaluated by analyzing the correlation of time-varying signals from two spatially distinct regions. Correlation analyses will also be performed (29, 43, 44). The objective is to compare alterations in brain functional networks across different groups and to examine changes in the strength of FC before and after treatment, thereby investigating the modulatory effects of TMS on brain networks.

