#### Exploratory outcomes

2.7.3

Alterations in brain FC (as measured by total integration) across various groups. Additionally, changes in the strength of FC before and after treatment will serve as exploratory outcome measures to explore the mechanisms underlying TMS treatment for ET. MRI will be conducted at baseline, on D10, and at W4.

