cTBS uses rapid pulse patterns to quickly inhibit targeted brain areas (51), while low-frequency rTMS provides more lasting effects, suitable for long-term modulation (52). We hypothesize that combining these TMS techniques can yield complementary benefits. Chuang et al. (32) found that cTBS suppresses motor cortex excitability in ET patients and reduces tremor amplitude. Batra et al. (33) showed that cTBS significantly improves tremor symptoms by increasing the contralateral silent period (cSP). Gironell et al. (25) and Popa et al. (29) reported tremor improvements after rTMS stimulation of the cerebellum. However, data on the effects of noninvasive brain stimulation techniques applied to the cerebellum and motor areas of ET patients show variability in their effects on tremor (53, 54). Specifically, there is a significant degree of variability among individuals. Olfati et al. (28) found no significant improvement in the overall tremor score with rTMS compared to sham stimulation on days 5, 12, or 30 after treatment. In contrast, Popa et al. (29), using the same stimulation protocol, observed a significant and lasting reduction in all aspects of tremor. It is important to consider that ET is a highly heterogeneous disorder with potential inter- and intra-individual differences, where factors such as anxiety (55), fatigue (56), and caffeine consumption (57) can all influence the severity of tremors. Furthermore, the placebo effect is a concern that should not be overlooked; Shin et al. (27) found that there was an improvement in tremor scale scores regardless of whether the stimuli were real or sham. The cerebellum and cortex are the most popular targets for stimulation in TMS studies aimed at treating ET. Previous findings suggest that the outcomes of TMS for ET are highly variable, and we speculate that the use of double-target stimulation may enhance the stability of treatment effects.

In this study, we will use Rs-fMRI to explore the alterations in brain functional connectivity before and after TMS treatment for ET, as well as to assess whether FC differs among three distinct groups. Studies have shown disruption in FC between the bilateral cerebellum and the cortex in patients with ET (58, 59). Furthermore, tremor severity may exhibit a positive correlation with FC between cerebellar lobule VI and VIM, as well as between the VIM and the cortex (60). These findings underscore the critical role of the CTC loop in the pathogenesis of ET.

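### Before-after change in functional connectivity is a separate mechanistic outcome with no stated contrast against change under sham, so a change shared by all arms could be reported as TMS modulation

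*Protocol article*

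**What the plan says.** The protocol article describes the FC analysis in three places, each time as two questions.

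- **Section 2.5 (Brain imaging).** The sentence opens with a between-group aim: "The objective is to compare alterations in brain functional networks across different groups". It then adds a second aim, to "examine changes in the strength of FC before and after treatment, thereby investigating the modulatory effects of TMS on brain networks".
- **Section 2.7.3 (Exploratory outcomes).** The first item is "Alterations in brain FC (as measured by total integration) across various groups". A further sentence, introduced as an addition, says that "changes in the strength of FC before and after treatment will serve as exploratory outcome measures to explore the mechanisms underlying TMS treatment for ET".
- **Section 6 (Discussion).** Resting-state fMRI will be used to explore "alterations in brain functional connectivity before and after TMS treatment for ET, as well as to assess whether FC differs among three distinct groups".

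A concurrent control exists. Section 2.3.3 says: "Patients assigned to the sham-stimulation group will receive sham stimulation targeting the left M1 cortex and the right cerebellar hemisphere". Section 2.1 and Table 1 schedule MRI at baseline, D10 and W4 without limiting it to any arm. Section 5 names generalized estimating equations for the primary and accelerometer outcomes and names no model for FC.

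**The concern.** To say that TMS modulates a network is to say that FC changed more under active stimulation than it would have changed without it. The sham arm supplies that comparison. A before-after comparison within an arm does not: its null hypothesis is zero change over time, and anything that moves FC between scans in every arm counts against that null.

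The article itself gives reason to take a shared change seriously. Section 6 warns of placebo response and notes that in one cited study "there was an improvement in tremor scale scores regardless of whether the stimuli were real or sham". The same section says that tremor severity may correlate with FC along the cerebello-thalamo-cortical pathway. If tremor improves under sham, FC could plausibly move under sham as well. That last step is an inference; the article reports no FC change under sham.

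Mechanism is also part of the hypothesis in the Introduction, which expects tremor relief through modulation of specific neural pathways. A mechanistic statement resting on uncontrolled change could be carried into the planning of the Phase 3 trial.

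**Working it through.** **Reading the passages together.** Sections 2.5, 2.7.3 and 6 all keep the group comparison and the before-after change apart. In 2.7.3 the mechanistic purpose is stated in the sentence on before-after change. None of the three sections says that this change is to be contrasted with change under sham.

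**No figure to reproduce.** The article gives no effect size, SD, drift or power for FC. Its only related number is the sample size, 3 × 8 = 24, which is consistent and is justified by precedent. What follows is therefore an illustration.

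**Inputs.**
- From the article: n = 8 per arm (section 2.8); two-sided 0.05 (section 5).
- Assumed: equal arms, normal change scores, a TMS effect on FC of exactly zero, and a shift *d* shared by all arms, in units of the SD of the change score, from 0 to 1.

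**Before-after test in one arm.** This is a paired t-test on 7 degrees of freedom with noncentrality d × √8. At d = 0.5 this is 0.5 × 2.828 = 1.414, and the probability of significance is 0.232.

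**At least one of two active arms.** 1 − (1 − 0.232)² = 1 − 0.590 = 0.41.

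**Significant in dual but not in sham.** 0.232 × (1 − 0.232) = 0.178.

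**Between-arm test on change, dual versus sham.** The shared shift cancels in the difference, so the error rate does not depend on *d*. Simulation (200,000 replicates) gave 0.050, 0.049 and 0.051 at d = 0, 0.5 and 1.0. A three-arm ANOVA on change gave 0.050, 0.050 and 0.052.

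| Shared shift (SD) | Before-after, one active arm | At least one of two active arms | Dual versus sham on change |
|---|---|---|---|
| 0 | 5% | 10% | 5% |
| 0.25 | 9% | 18% | 5% |
| 0.5 | 23% | 41% | 5% |
| 0.75 | 45% | 70% | 5% |
| 1.0 | 68% | 90% | 5% |

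The 10% in the first row is only the effect of testing two arms; each test is at its nominal 5%.

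**What the between-arm contrast costs.** For a true 1-SD change confined to the dual arm, its noncentrality is 1 × √(8/2) = 2 on 14 degrees of freedom, giving power of 0.46. The one-arm before-after test has 0.68. That same 0.68 is its rate of significance when a 1-SD change is shared by all arms and TMS does nothing, so the extra sensitivity comes without the ability to tell the two situations apart.

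**The case against.** The strongest reply is that the group comparison is planned and comes first. In section 2.5 the closing clause about modulatory effects follows both halves of the sentence, so the comparison across arms is part of the stated basis. A reader who sees only the second half might infer that the plan draws mechanism from uncontrolled change alone. The text does not support that.

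Nor does the article state a test, a null hypothesis or a decision rule for FC. Examining change in all arms alongside a group comparison is compatible with a group-by-time analysis, and the choice of model may properly sit in an analysis plan that is not shown. It would be wrong to say that a shared change *will* be reported as mechanism, or that significance in dual without significance in sham is a planned criterion.

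Two further readings go too far. One takes the Discussion phrase "as well as to assess whether FC differs among three distinct groups" to mean that arms are compared on FC level; the Methods speak of alterations across groups, which more naturally means change, although the wording leaves it open. The other invokes regression to the mean, which is weakly supported because the eligibility criteria do not select on FC. The cited sham response also concerns tremor scores, not FC.

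What remains is narrower. Planning a group comparison does not cure a separate before-after outcome that is given its own mechanistic meaning. This is not a complaint about a missing model: section 2.7.3 states an outcome and the purpose it serves, and that outcome on its own cannot serve it.

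**Conclusion.** The point holds as a minor one. The plan contains a between-group FC comparison, but it also lists before-after FC change as a separate outcome for exploring modulation and mechanism, with no contrast against sham. A change shared by active and sham arms could therefore be reported as a TMS effect.

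The size depends wholly on how large a shared change is, and the documents do not say. At an assumed 0.5 SD, with 8 per arm and no TMS effect, the one-arm test is significant in about 23% of trials against about 5% for the between-arm test; with no shared change there is no excess.

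Severity is low because FC is exploratory, the trial is a pilot, and neither the primary nor the secondary outcomes depend on it.

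**What to change.** - **Sections 2.5 and 2.7.3:** state that conclusions on modulation or mechanism rest on the between-arm difference in FC change (dual versus sham and single versus sham), from baseline to D10 and from baseline to W4. Adjustment for baseline FC is preferable but not essential to the correction.
- **Same sections:** state that before-after change within an arm is descriptive only.
- **Section 6:** reword the group question so that it asks whether the change in FC differs among groups.

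The cost is wording; the schedule already includes the scans and no further patients are needed. The downside is sensitivity: about 46% power against 68% for a 1-SD change confined to the dual arm, before any gain from baseline adjustment. With 8 per arm the between-arm contrast reaches 80% power only at a true difference of about 1.5 SD, so estimates with confidence intervals will be more informative than significance.
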